#### **8.1.2.2 Antiretroviral Therapy Toxicity and Management**

Patients will be closely monitored for signs and symptoms of study drug toxicity. For all toxicities that require either temporary or permanent discontinuation of study therapy, relevant clinical and laboratory tests will be obtained as clinically indicated until final resolution or stabilization of the toxicity. Symptoms and laboratory findings will be graded by severity using the NIAIDS/ACTG Toxicity Tables (Appendices IV and V).

The study will use antiretroviral medications that have known and well-described toxicity profiles. The diagnosis and management of the major adverse events and toxicities are described below:

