EFV or NVP may be held at the investigator’s discretion until the cutaneous toxicity returns to Grade <1, at which time EFV therapy should be reinstituted at full dose. If NVP is held > 7 days, NVP should be reinstituted with the lead-in dose of 200 mg QD for 2 weeks, then 200 mg BID. If a Grade 2 cutaneous/allergic reaction recurs, the medical officer should discuss with the study investigators whether the subject should be further re-challenged. The subject should be closely monitored for recurrence of the rash, HSR, clinical hepatitis, or isolated changes in LFTs. If any of these conditions develop on NVP, the subject should immediately and permanently discontinue NVP. For subjects on NVP, if resolution takes more than 2 weeks, contact the study investigators.

If the rash is considered to be most likely due to concomitant illness or medication, standard management, including discontinuation of the likely causative agent, should be undertaken. If no other causative factor is found after clinical evaluation, the subject should be treated symptomatically until the rash resolves.

For Grade 3 rash, subjects should hold all study drugs.Upon resolution to Grade <1, the investigator should discuss at a study conference call with senior investigators whether re-challenge is appropriate. If the Grade 3 rash is considered to be most likely due to concomitant illness or medication, standard management, including discontinuation of the likely causative agent, should be undertaken.

For Grade 4 rash, (e.g., exfoliation, mucosal involvement, or target lesions [erythema multiforme]) or any evidence of Stevens-Johnson syndrome, subjects should discontinue all study drugs.

For grade ≥ 3 rash, do not substitute EFV for NVP or NVP for EFV

In the event that Grade 2 or 3 rash fails to resolve after 14 days, increases in severity, is associated with systemic (fever, malaise, nausea) or allergic (e.g., urticaria) symptoms, or is associated with mucosal or target lesions, all study drugs should be held until symptom resolution. NVP has been rarely associated with the development of severe rash, including SJS and toxic epidermal necrolysis (TEN). A new onset prodromal syndrome consisting of clinical symptoms manifested as fever (>39°C), malaise, cough, lymphadenopathy, edema, myalgia, and/or arthralgia may occur prior to the development of cutaneous manifestations of SJS, TEN, or the SJS/TEN overlap syndrome.

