### **8.1.4 Discontinuation and Re-initiation of Antiretroviral Therapy**

#### **8.1.4.1 Definitions**

To hold study drug means to temporarily withhold the use of one or all medications. When a study drug is held, it may be re-started as clinically indicated.

To discontinue study drug means to stop one, or more, study medications without the intent of restarting the medication. It is a synonym for permanent discontinuation of treatment. A study medication may first be held during the evaluation of a patient before a decision is made to discontinue the medication.

To restart study drug means to provide again a study medication that was previously held in a patient.

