**PARAMETER GRADE 1 GRADE 2 GRADE 3 GRADE 4**

MILD MODERATE SEVERE POTENTIALLY LIFE THREATENING

Neuro-sensory Mild impairment (dec Mod impairment (mod Severe impairment Sensory loss involves

sensation, e.g., dec sensation, e.g., (dec or loss of limbs and trunk.

vibratory, pinprick, vibratory, pinprick, sensation to knees or

hot/cold in great toes) hot/cold to ankles) wrists) or loss of

in focal area or and/or joint position sensation of at least

symmetrical distri- or mild impairment mod degree in multiple

bution that is not different body areas

symmetrical (i.e., upper and lower

extremities)

URINALYSIS

Proteinuria

Spot urine 1+ 2 - 3+ 4+ Nephrotic syndrome

24 hour urine 200 mg-1 g loss/day OR >1 - 2 g loss/day OR >2 - 3.5 g loss/day OR Nephrotic syndrome OR

<0.3% OR 0.3 - 1.0% OR >1.0% OR >3.5 g loss/day

<3 g/l 3 - 10 g/l >10 g/l

Gross Hematuria Microscopic only Gross, no clots Gross plus clots Obstructive OR

transfusion req

MISCELLANEOUS

Fever 37.7 - 38.5C OR 38.6 - 39.5C OR 39.6 - 40.5C OR >40.5C OR

oral >12 hours 100.0 - 101.5F 101.6 - 102.9F 103 - 105F >105F

Headache Mild; no Rx req Mod; or non-narcotic Severe; OR responds to Intractable; OR requiring

analgesia Rx initial narcotic Rx repeated narcotic Rx

Allergic Reaction Pruritus without Localized urticaria Generalized urticaria Anaphylaxis

rash angioedema

Cutaneous/Rash/ Erythema, pruritus Diffuse maculopapular Vesiculation OR moist ANY ONE: mucous membrane

Dermatitis rash OR dry desquamation OR involvement, suspected

desquamation ulceration Stevens-Johnson (TEN),

erythema multiforme, necrosis req surgery/ exfoliative dermatitis

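### Section 8.1.2.2.6 grades rash with mucosal or target lesions as 4 and stops all study drugs for good, then treats the same lesions as Grade 2 or 3 and only holds the drugs

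*Protocol*

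**What the plan says.** Protocol Section 8.1.2.2.6 sets out rash management by grade. Its Grade 4 rule gives exfoliation and the two lesion types as examples and orders a complete stop: "mucosal involvement, or target lesions [erythema multiforme]) or any evidence of Stevens-Johnson syndrome, subjects should discontinue all study drugs".

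Two paragraphs later the section turns to Grade 2 or 3 rash. It lists the circumstances in which all drugs are to be withheld: no resolution within two weeks, worsening, systemic or allergic symptoms, and finally the same lesions: "or is associated with mucosal or target lesions, all study drugs should be held until symptom resolution".

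Section 8.1.4.1 defines the two actions. On a hold it says "When a study drug is held, it may be re-started as clinically indicated". On discontinuation it says "It is a synonym for permanent discontinuation of treatment". It also allows one to precede the other: "A study medication may first be held during the evaluation of a patient before a decision is made to discontinue the medication".

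Section 8.1.2.2 fixes how severity is decided: "Symptoms and laboratory findings will be graded by severity using the NIAIDS/ACTG Toxicity Tables". Those tables are Appendices IV and V. In Appendix IV, the row for cutaneous events, rash and dermatitis contains "Vesiculation OR moist ANY ONE: mucous membrane" and, further along the same row, "erythema multiforme, necrosis req surgery/ exfoliative dermatitis".

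**The concern.** One clinical finding receives two grades and two actions within a single section, and the actions end differently. Under the Grade 4 rule the drugs are not given again. Under the last paragraph they are withheld until symptoms resolve, and what happens next is left open.

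Medical officers apply this text while treating a patient. The same section warns that nevirapine has rarely caused Stevens-Johnson syndrome and toxic epidermal necrolysis. If an officer follows the last paragraph and records such a rash as Grade 2 or 3, re-exposure to the suspected drug remains possible after lesions that the Grade 4 rule treats as ending treatment.

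**Working it through.** No arithmetic applies. The check sets the provisions side by side.

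1. **Same lesions.** The Grade 4 rule names mucosal involvement and target lesions, with erythema multiforme given in brackets as the meaning of the latter. The hold clause names mucosal or target lesions. Both refer to the same findings.

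2. **Different actions.** The Grade 4 rule discontinues; the last paragraph holds. Section 8.1.4.1 defines both words, one as permanent and one as temporary, so the difference cannot be put down to loose wording.

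3. **Which grade is right.** Section 8.1.2.2 sends grading to the toxicity tables. The cutaneous row of Appendix IV was flattened when the text was extracted, so the columns have to be read from word order. On that reading, mucous membrane involvement opens the any-one list of Grade 4 criteria. Suspected Stevens-Johnson syndrome and erythema multiforme belong to the same list. The Grade 4 examples in Section 8.1.2.2.6 agree independently, so the conclusion does not rest on the damaged table alone. Under the protocol's grading, a rash with these lesions is Grade 4, and the Grade 2 or 3 case described in the last paragraph should not arise.

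4. **Can a hold be the first step of a discontinuation?** Section 8.1.4.1 permits this while a patient is being evaluated. Section 8.1.2.1.2 likewise holds suspect agents for any grade III or IV event pending evaluation. The hold in Section 8.1.2.2.6 ends at a different point, the resolution of symptoms rather than the completion of an evaluation. For these lesions the Grade 4 rule has also already made the decision.

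5. **Where the hold can lead.** For Grade 3 rash, Section 8.1.2.2.6 sends the resolved case to a conference call that considers re-challenge. Section 8.1.4.2.3, item 1, allows a drug to be restarted after an adverse event has subsided to grade II or less. A rash recorded as Grade 2 or 3 can therefore reach a re-challenge decision.

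6. **What stands in the way.**
   - Section 8.1.2.2.6 requires discontinuation on any evidence of Stevens-Johnson syndrome. It also stops nevirapine permanently after severe rash.
   - Section 8.1.2.1.2 generally discontinues medication for symptomatic grade III/IV events.
   - Section 8.1.4.2.2 generally does so for grade III and IV serious adverse events and lists hypersensitivity as a ground.
   - Section 8.1.4.2.3, item 2, bars restart after an allergic or hypersensitivity reaction.
   - Section 8.1.4.2 requires any restart to be discussed with a Principal Investigator or designee.

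   The general rules are qualified and do not reach a rash labelled Grade 2. The bar on restart depends on the event being judged allergic. The required discussion would be guided by a section that gives both answers.

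**The case against.** The best defence is that the clause is redundant rather than dangerous. If these lesions always make a rash Grade 4, the clause has no valid cases and the explicit Grade 4 rule governs. The last paragraph can also be read as covering a rash first graded 2 or 3 that then evolves: all drugs stop at once and are discontinued when the rash is regraded. Nothing in the hold sentence orders a restart, and the provisions in step 6 of the working stand behind it.

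Much of this is fair, and it limits the point. It does not remove it. The clause attaches a lower grade to lesions that define Grade 4, and it sets an end to the hold that the Grade 4 rule does not allow. A clause with no valid cases can still lead an officer to choose the lower grade.

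A reader might infer three stronger things that the documents do not support:

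- That the protocol directs efavirenz to be restarted at full dose after such lesions. That instruction belongs to a hold made at the investigator's discretion, earlier in the section, and does not govern the mandatory hold of all drugs.
- That re-exposure is unrestricted. Step 6 shows otherwise.
- That the nevirapine rules in the same section also conflict with its re-challenge wording. They can be obeyed together, so no precedence rule is needed.

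**Conclusion.** The text is wrong as written: it is an internal inconsistency in a safety rule, and it should be corrected. The practical gap is limited to rash with mucosal or target lesions when Stevens-Johnson syndrome is not recognised, the rash is handled under the Grade 2 or 3 paragraph, and the event is not judged allergic. It arises in patients taking efavirenz or nevirapine, which in Step 2 are substitutes for components of Trizivir (Section 5.2.1.4).

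The protocol states no rash rate, so no count of affected patients can be given. The conclusion assumes that the flattened Appendix IV row is read correctly, and the Grade 4 examples in Section 8.1.2.2.6 support that reading. The primary outcome, the sample size and the analyses are untouched.

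**What to change.** In the last paragraph of Section 8.1.2.2.6, delete the item on mucosal or target lesions from the list of reasons to hold, and move the conjunction in front of the item on systemic or allergic symptoms. The hold then applies to a Grade 2 or 3 rash that persists, worsens, or comes with systemic or allergic symptoms. Add to the Grade 4 rule: *Any rash with mucosal or target lesions is Grade 4.*

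The cost is one deleted clause, one added sentence and a note to the medical officers, handled as an amendment under Section 11.6. The change adopts the grading that the section and Appendix IV already use, so it brings in no new clinical policy. Visits, sample size and analysis stay as they are.

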##### 8.1.2.2.7 Liver Toxicity and Nevirapine

Women with CD4+ cell counts >250 cells/µL, including pregnant women receiving chronic treatment for HIV infection, are at considerably higher risk (12-fold) of hepatotoxicity. Some of these events have been fatal. This subset of patients was identified by analyses of CD4 count at the time of initiation of NVP therapy. The greatest risk of severe and potentially fatal hepatitis events (often associated with rash) occurs in the first 6 weeks of NVP treatment. Men with CD4+ cell counts >400 cell µL at initiation of NVP therapy have a 3-fold higher risk of hepatoxicity compared to men with CD4+ cell counts ≤ 400 cells/µL. However, the risk continues after this time and patients should be monitored closely for the first 20 weeks of treatment with NVP. In some cases, hepatic injury progresses despite discontinuation of treatment. For grade ≥3 rash or hepatitis, do not substitute EFV for NVP.

Female subjects with CD4>250 and male subjects with CD4>400 should not be started on nevirapine. Subjects taking NVP should be monitored for the development of signs and symptoms of hepatitis, which include fatigue, malaise, anorexia, nausea, acholic stools, bilirubinuria, jaundice, liver tenderness, or hepatomegaly, with or without initially abnormal serum transaminase levels at weeks 2, 4 and monthly for the first 20 weeks from initiation. After the initial 20-week period, clinical and laboratory monitoring should continue every 2 to 3 months throughout NVP treatment. Subjects with these signs and symptoms must be advised to hold NVP and seek medical attention immediately and have LFTs performed. If the physician determines that the subject has clinical hepatitis with or without LFT abnormality, and there is any possibility NVP is the cause, NVP should be discontinued and not restarted after recovery.

##### 8.1.2.2.8 Immune Reconstitution Inflammatory Syndrome to TB (Paradoxical Reactions)

Any potent ARV regimen can produce transient worsening of clinical TB symptoms after initial response to antituberculous therapy. Up to one third of TB patients treated with potent ARV may develop immune reconstitution inflammatory syndrome (IRIS) to TB (paradoxical reactions).52 The most common manifestations include fever and worsening lymphadenopathy, but, occasionally, worsening pulmonary infiltrates is observed. Typically, the syndrome occurs 1-3 weeks after initiation of ARV and is self-limited. A brief course of corticosteroids is sometimes used to control exuberant reactions and will be permitted in the study. For further details see section 6.3.3 and Appendix VI.

### **8.1.3 Management of Virologic Failure**

Virologic failure is defined as confirmed HIV RNA > 200 copies/ml after six months of antiretroviral therapy and no evidence of non-adherence. Since the punctuated therapy lasts only six months, virologic failure will not necessitate a change in antiretroviral therapy in most instances. If, however, a subject reaches a primary study outcome during punctuated therapy, then an alternative regimen with minimal cross-drug resistance will be selected from available antiretroviral medications. For all patients on antiretroviral therapy, virologic failure will prompt a review of the clinical status of the patient using CD4+ count, physical examination, and laboratory test as indicated. If clinically indicated an alternative regimen with minimal cross-drug resistance will be selected from available antiretroviral medications. When virologic failure is diagnosed, patterns of drug resistance will be performed to guide future choice of treatment. If an effective antiretroviral regimen is not available, then antiretroviral medication will be discontinued.

For further details see Sections 5.2.1.4, 8.1.4.2.2, 10.2.2.3.

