### **6.3.2 Development of ARV drug resistance**

Viral drug resistance will be examined in specimens from patients with confirmed failure to suppress HIV RNA < 200 copies/ml after the six month course of antiretroviral therapy on step 2 or after six months of antiretroviral therapy on Step 3, and, for a random subset of 20 patients 2 months after completing punctuated therapy. In these patients, pre-treatment plasma will also be assayed for drug resistance. Genotypic analysis performed at the Joint Clinical Research Center Virology laboratory will be used to evaluate for drug resistance. Resistance will be defined according to IAS/USA guidelines.

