##### 8.1.4.2.2 Criteria for Discontinuing Antiretroviral therapy

At any time during treatment with antiretroviral therapy, antiretroviral medication may be discontinued for conditions described in Section 8.1.2, or for any other serious adverse event that may be related to the use of medication. In general, grade III and IV serious adverse events will result in discontinuation of one or more antiretroviral medications. For adverse events of grade I or II, antiretroviral therapy will be discontinued if the adverse event recurs when drug is re-started or when the adverse event worsens after dose adjustment.

Drug may be discontinued under the following circumstances:

- Allergic hypersensitivity reaction to study drug.
- Development of a toxicity that warrants permanent discontinuation of any study drug
- Recurrence of treatment-limiting toxicity on re-challenge will result in permanent discontinuation of the putative responsible drug.
- Confirmed virologic failure (HIV RNA > 200 copies/ml after six months of treatment) and no remaining alternatives for antiretroviral therapy (Section 8.1.3).
- Request by the subject to withdraw.
- The patient refuses further therapy.
- Failure or inability to comply with antiretroviral therapy
- Clinical reasons believed life threatening by study investigators, even if not addressed in the toxicity management of the protocol.
- Subject judged by the investigator to be at significant risk of failing to comply with the provisions of the protocol as to cause harm to self or seriously interfere with the validity of the study results.
- Termination of the study.
- Withdrawal of the study drug(s) at the request of the sponsor.
- Requirement for prohibited concomitant medications (see Table 8)

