#### **10.2.2.3 Specific Aim 3**

To determine whether a punctuated six-month course of highly active ARV therapy is safe when given with anti-tuberculosis therapy as measured by development of ARV drug resistance, toxicity and side effects, and paradoxical reactions.

Safety

The safety of the study interventions, including adverse events and paradoxical reactions will be examined by summarizing the proportion, or rate, of these events according to each study arm. We will compare the cumulative proportion of grade III/IV adverse reactions and paradoxical reactions between study arms with the chi-square or Fisher’s exact test. Time until first event will also be examined using Kaplan-Meier analysis with log-rank test to compare arms. Because an individual may have more than one adverse event, we will also estimate the incidence density of adverse events in each study arm and compare these rates by determining the relative risk of adverse events (with 95% confidence intervals) in the group receiving intervention compared with the reference group.

Viral drug resistance

Descriptive analyses of drug resistance mutations in reverse transcriptase will be performed. Based on HIV RNA patterns and values, samples will be assayed from patients who exhibit viral rebound during the punctuated therapy phase and, for a subset of 20 patients 2 months after completing punctuated therapy. If resistance is identified in samples off therapy, we will assay the plasma for persistence of the mutations. We will also assess drug resistance in all specimens from patients who exhibit virologic failure (confirmed HIV RNA >200 copies/mlafter 6 months of therapy, Section 8.1.3) during the continuation phase (Step 3). Proportions and rates of drug resistance will be compared between the 2 strategies.

Analysis of Additional Outcomes

Analysis when CD4+ < 250/µL and Continuous ARV Therapy Begun

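### The population for the Step 3 resistance endpoint is contradictory: Section 8.1.3 requires no evidence of non-adherence, Section 6.3.2 and the Step 3 schedule do not, and Section 10.2.2.3 can be read either way

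*Protocol*

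**What the plan says.** Four parts of the protocol bear on who is tested for resistance in Step 3.

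- **Section 6.3.2** defines the resistance outcome: "Viral drug resistance will be examined in specimens from patients with confirmed failure to suppress HIV RNA < 200 copies/ml after the six month course". The same criterion covers Step 3 once six months of ARV have been taken there, and a random sample of 20 patients from the punctuated arm is added. Adherence is not mentioned.
- **Appendix I, Step 3 schedule, footnote j** requires genotyping of patients who have not suppressed below 200 copies/mL after six months of ARV, again without an adherence condition. The row it belongs to, and the matching item in Section 7.4.2, list genotyping only as clinically indicated.
- **Section 8.1.3** holds the only formal definition: "Virologic failure is defined as confirmed HIV RNA > 200 copies/ml after six months of antiretroviral therapy and no evidence of non-adherence". It continues: "When virologic failure is diagnosed, patterns of drug resistance will be performed to guide future choice of treatment". It also refers the reader to 10.2.2.3.
- **Section 10.2.2.3** describes the Step 3 analysis: "We will also assess drug resistance in all specimens from patients who exhibit virologic failure". The parenthesis that follows gives confirmed HIV RNA above 200 copies/ml after six months of therapy and cites Section 8.1.3. It then says: "Proportions and rates of drug resistance will be compared between the 2 strategies".

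Section 8.1.4.2.2 also cites 8.1.3 and likewise restates only the RNA criterion.

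**The concern.** ARV drug resistance is part of the safety objective in Section 2.2. It is also one of three major outcomes in the analysis of whether punctuated therapy jeopardizes later continuous ARV (Section 10.2.2.3, additional outcomes). Who enters that endpoint should not depend on which section the analyst opens.

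The adherence clause matters because of how Step 3 is run. Therapy there is self-administered. Section 7.4.2 provides for unannounced home visits, pill counts and adherence questionnaires from month 1. Evidence of non-adherence is therefore actively sought, yet 8.1.3 does not say how much of it disqualifies a patient. If the clause were applied, membership of the endpoint population would rest on a judgement made after randomization in an open-label trial. One arm would already have had six months of modified directly observed ARV (Section 5.2.4), so a difference in Step 3 adherence between arms is possible, although nothing in the protocol shows it.

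**Working it through.** The protocol states no expected resistance, viraemia or non-adherence rate, so there is no figure to reproduce. The check is a comparison of texts, followed by an illustration on assumed values.

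**1. The texts side by side**

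| Place | RNA criterion | Adherence condition | Role |
|---|---|---|---|
| 6.3.2 | confirmed failure to suppress below 200 after six months, Step 2 or Step 3 | none | outcome definition |
| Appendix I Step 3, footnote j | failure to suppress below 200 after six months | none | schedule |
| 8.1.3 | confirmed above 200 after six months | no evidence of non-adherence, no threshold | management; triggers resistance testing |
| 8.1.4.2.2 | confirmed above 200 after six months | not restated, cites 8.1.3 | stopping criteria |
| 10.2.2.3 | confirmed above 200 after six months | not restated, cites 8.1.3 | analysis |

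**2. One hypothetical record.** A Step 3 patient has HIV RNA of 20,000 copies/ml at months 6 and 12, and a pill count shows missed doses.

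- Under 6.3.2 and footnote j, the patient is genotyped and counted.
- Under 8.1.3, the patient is not a virologic failure, and that section does not call for the test.
- Under 10.2.2.3, the patient is in if the printed criterion governs and out if the cited definition governs.

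**3. What applying the 8.1.3 clause would do.** Let f be the share of confirmed-viraemic Step 3 patients with evidence of non-adherence. Let k be resistance prevalence in those patients divided by its prevalence in the other viraemic patients. Both are assumptions.

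- Share of resistant cases missed = f·k / ((1 − f) + f·k)
- Proportion resistant among those genotyped, relative to all viraemic patients = 1 / ((1 − f) + f·k)

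| f | k | Resistant cases missed | Relative proportion among genotyped |
|---|---|---|---|
| 0.10 | 0.5 | 0.05/0.95 = 5% | 1.05 |
| 0.10 | 1.0 | 0.10/1.00 = 10% | 1.00 |
| 0.10 | 1.5 | 0.15/1.05 = 14% | 0.95 |
| 0.30 | 0.5 | 0.15/0.85 = 18% | 1.18 |
| 0.30 | 1.0 | 0.30/1.00 = 30% | 1.00 |
| 0.30 | 1.5 | 0.45/1.15 = 39% | 0.87 |
| 0.50 | 0.5 | 0.25/0.75 = 33% | 1.33 |
| 0.50 | 1.0 | 0.50/1.00 = 50% | 1.00 |
| 0.50 | 1.5 | 0.75/1.25 = 60% | 0.80 |

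The count falls whenever f and k are above zero. The proportion among those genotyped rises when k is below 1, is unchanged at k = 1, and falls when k is above 1.

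**4. Between arms.** If f and k are equal in both arms, the ratio of the arms is unaffected. Suppose instead that k = 1 and f is 0.10 in one arm and 0.30 in the other. Resistant cases per Step 3 starter are then retained at 0.90 and 0.70, so a true ratio of 1 would appear as 0.70/0.90 = 0.78. At k = 1 the proportion among those genotyped would stay unbiased. At k = 1.5 it would be distorted by 0.870/0.952 = 0.91.

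**The case against.** The strongest reply is that nothing is actually lost. Section 10.2.2.3 prints its own criterion, and it is RNA only; on those words the patient in the record above is assayed. Section 6.3.2 is the section that defines the outcome, and footnote j says that genotyping will be done. Section 8.1.3 is a management section: it calls for a test when failure is diagnosed and does not forbid testing other viraemic patients. Plasma is stored through Step 3 whatever the adherence (Section 7.4.2).

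Much of this stands. A reader might infer that the Step 3 analysis uses the narrower definition, that partly adherent viraemic patients are dropped from genotyping, and that resistance is therefore under-counted. The documents do not establish any of these, because the pointer to 8.1.3 sits beside a criterion that omits the clause.

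A reader might also put a size on it. If 30 to 60% of viraemic patients showed missed doses, 1 − 0.6 = 40% to 1 − 0.3 = 70% of resistant cases would remain. That range rests on rates with no source in the protocol, on equal resistance in both groups, and on a denominator of all Step 3 starters, which 10.2.2.3 does not state.

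The reply does not remove the conflict. Section 8.1.3 is the only formal definition, it ties testing to that diagnosis, and 8.1.3 and 10.2.2.3 cite each other. Apart from footnote j, the schedule entries leave genotyping to clinical indication, and the clinical rule is the one in 8.1.3. A site or analyst could follow that route in good faith.

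**Conclusion.** The contradiction holds. Section 8.1.3 carries an adherence condition that 6.3.2 and footnote j lack, and 10.2.2.3 cites the narrower text while wording the broader one. The population for the Step 3 resistance endpoint is therefore not fixed.

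The consequences are conditional on the 8.1.3 definition being applied:

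- The count of resistant cases can only fall.
- The proportion among those genotyped can move in either direction.
- The comparison between arms can be biased if the exclusion, or resistance among those excluded, differs by arm.

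No size can be derived from the protocol; the tabulated values show direction and range under assumed f and k only. The point is worth correcting because it concerns a stated safety endpoint and the correction is small.

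**What to change.** Analysis text only:

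1. State in 10.2.2.3 that the resistance endpoint population is that of 6.3.2: all patients with confirmed HIV RNA above 200 copies/ml after six months of ARV, regardless of adherence.
2. State the denominator of the resistance proportions, for example all Step 3 starters with six months of follow-up.
3. Report adherence as a descriptor of these patients.
4. Remove the pointer to 8.1.3, or qualify it as referring to the RNA criterion only.

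The sponsor should also reconcile 8.1.3 with 6.3.2, footnote j and the schedule entries that leave genotyping to clinical indication. How 8.1.3 is used in clinical management is for the sponsor to decide.

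The cost is a short edit to 10.2.2.3, with no genotypes beyond those 6.3.2 and footnote j already plan.
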